#### Warm-up and cool-down

Before starting exercises, participants will be taken through a group warm up session, followed by a cool down session at the end of exercises, each lasting 10–15 min. Warm up is aimed at readying the body for both the physical aspects of performance (increased blood flow and muscle temperature) and mental readiness for exercise while cool down session facilitates a smoother decline in temperature and blood flow^20^ Both warm up and cool down will consist of stretching and flexibility exercises during which participants will perform both upper and lower body flexibility exercises, held for 10–15 s each (including stretching of major muscle groups such as the calves, hamstrings, quadriceps and biceps, as well as range of motion exercises for the neck, shoulders and trunk), 2 days/week.^13^ The cool down session has the same activities of warm-up (online supplemental table 1) but performed at a slower pace.

10.1136/bmjopen-2020-047641.supp1Supplementary data

#### Endurance training

Each participant will go through two stations of endurance exercise; load-adjustable stationary cycling and ground-based walking stations. We shall employ an intensity of continuous exercise at each station for 10 min or until a Borg dyspnoea score of 4–6 (moderate to (very) severe) is attained.^21 22^ Participants who may have difficulty in sustaining continuous high-intensity exercise will have interspersed periods of rest or lower intensity exercise to maximise the benefits of exercise training.^13^ The walking exercise regime will be individually prescribed to participants based around their performance in the ISWT. Participants will be encouraged to walk at 85% of their maximal ISWT walking speed.^23^

#### Strength training

Each participant will go through two stations for strengthening upper limb muscles (pull-ups and biceps curls) and two for strengthening lower limb muscles (sit-to-stand and step-up exercises). Each of the stations will include 3 sets of 8–12 repetitions. Participants will be asked to continue doing both endurance and resistance exercises at home, unsupervised.

### Education sessions

A dedicated education session will be conducted at the start of each class, before the exercise regimes (box 1; 12 sessions in total).

Box 1Education content of the Global RECHARGE Pulmonary Rehabilitation programmeNormal anatomy and physiology of the lungs.Pathophysiology of chronic lung disease.Tuberculosis and how it causes lung damage.Coping with chronic lung disease and coping with stress.Avoidance of risk factors for chronic lung disease.Early recognition and treatment of exacerbations.Strategies for managing breathlessness.Energy conservation during activities of daily living.Role and rationale for medications and devices.Benefit of exercise and physical activities.Healthy food intake.Secretion clearance techniques.

### Study outcomes

#### Primary outcome

The primary outcome is change in walking distance measured by the ISWT from preintervention to postintervention. A group change of at least 35 m is considered clinically important.^18^

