### Sample size

The study will be powered to detect a 35 m difference in the ISWT measured at baseline and after completion of PR.^18^ Assuming that ISWT follows an approximately normal distribution, a power calculation based on a paired t-test was performed. Based on a trial sample size of 40 participants in each of the treatment and control groups, a two-sided 5% significance level and a statistical power of 80%, the clinically important change in ISWT of 35 m will also be statistically significant. Our recent feasibility study^15^ was used to obtain an estimate of the pooled SD for the power calculation. Conservatively assuming up to 30% losts to follow-up at 6 weeks, a total of 114 participants are required to be recruited and randomised (1:1) to each arm (PR: 57 participants or waiting list: 57 participants). Using the 70% ineligibility rate during screening from the feasibility study, we will need to screen approximately 543 PTBLD patients.

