### Treatment arms

#### Usual care (control arm)

The participants in the waiting-list (control) arm will receive usual care and will be offered PR after completing 12 weeks of follow-up. There are currently no guidelines for the clinical management of PTBLD both locally and internationally. Usual care will be optimised where possible and will include the following: frontal chest radiograph, spirometry to screen for airway diseases, inhalational therapies for airway disease amenable to treatment (where appropriate), antibiotic and systemic glucocorticoid therapy for infective exacerbations (where appropriate), and verbal advice to quit smoking and reduce exposure to biomass smoke. According to local practice, all post-TB patients with significant postbronchodilator response on Spirometry (at least 12% and 200mls increase in forced expiratory volume in 1 s (FEV1)) are managed with a combination of inhaled corticosteroids and long-acting beta-agonists, while those with fixed airflow obstruction (postbronchodilator FEV1/forced vital capacity ratio of less than 0.70) are managed with long acting bronchodilators. PR will be offered as an adjunctive non-pharmacological treatment as recommended by international guidelines.^19^

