#### Incremental Shuttle Walking Test

The ISWT is frequently used as an outcome measure for PR.^24^ Improvement in walking distance of 35 m during the post-PR shuttle test, measured from baseline (pre-PR) using the ISWT is considered a clinically important difference.^18^ The ISWT requires the patient to walk up and down a 10 m course, identified by two cones inset 0.5 m from either end to avoid the need for abrupt changes in direction. The speed at which the patient walks is dictated by an audio signal played on an audio device. Each participant will receive standardised instructions to: ‘Walk at a steady pace, aiming to turn around when you hear the signal. You should continue to walk until you feel that you are unable to maintain the required speed without becoming unduly breathless’.^25^ To ensure the learning effect is accounted for, a practice ISWT will be performed and the participant will receive encouragement from the physiotherapist throughout the test in an effort to increase the distance one can walk. The test is terminated when either (1) the patient indicates that they are unable to continue, (2) if the operator determines that the patient is not fit to continue or (3) the operator assesses that the patient was unable to sustain the speed and cover the distance to the cone prior to the beep sounding.^25^

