### Data analysis

All randomised participants will be included in the intention to treat analysis population. The primary efficacy analysis will be based on both per protocol and modified intention-to-treat populations. For the primary analysis, the differences in the primary outcome (walking distance on the ISWT) with the corresponding two-sided 95% CI and p value will be estimated using a stratified analysis; a p<0.05 will be the measure for statistical significance. Predictive analytics software (SPSS^16^) will be used to analyse the data. Continuous data will be presented as mean and SD or median and IQRs, while categorical data will be presented as frequencies and percentages. All data will be assessed for normality and appropriate parametric and non-parametric tests will be used. Categorical variables between the two treatment groups will be compared using χ^2^ and Fisher’s exact test as appropriate. Continuous variables will be compared using t-test for normally distributed data and Mann-Whitney-U test for non-normally distributed data. Any baseline differences will be adjusted for. Both intention-to-treat and per-protocol analyses will be conducted after imputing any missing data. There will be no formal interim analysis of data. The final analysis will be performed when all the 114 participants have completed the last study related visit or previously withdrawn from the trial. We will fit linear mixed models for both per-protocol and intention-to-treat analyses.

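### The 35 m benchmark is worded as a pre-to-post change, while the trial's comparison is between arms, so the label of clinical importance and the powering do not match the primary contrast

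*Protocol article*

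**What the plan says.** Three sections of the protocol article give the 35 m figure, each time as a change over time.

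- **Primary outcome:** "The primary outcome is change in walking distance measured by the ISWT from preintervention to postintervention", followed by "A group change of at least 35 m is considered clinically important".
- **Incremental Shuttle Walking Test:** "Improvement in walking distance of 35 m during the post-PR shuttle test, measured from baseline (pre-PR) using the ISWT is considered a clinically important difference".
- **Sample size:** "The study will be powered to detect a 35 m difference in the ISWT measured at baseline and after completion of PR", and "a power calculation based on a paired t-test was performed".

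The comparison itself is described elsewhere. Study design sets PR against usual care in a 1:1 randomised trial. Data analysis promises "the differences in the primary outcome (walking distance on the ISWT) with the corresponding two-sided 95% CI and p value", without naming the arms in that sentence; the t-test, Mann-Whitney and mixed-model text around it implies a comparison of arms. Secondary outcomes states a between-arm comparison explicitly and includes the ISWT among its measurements. No section connects 35 m to the PR-minus-usual-care difference.

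**The concern.** A randomised control arm is there to remove the gain that would have occurred without PR. If the test is between arms but the 35 m yardstick is applied to the PR arm's change from its own baseline, the control arm informs the p value and drops out of the statement about clinical importance. A between-arm difference below 35 m could then be reported as both significant and clinically important.

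Some gain without PR is plausible. The control-arm section says "Usual care will be optimised where possible and will include the following", and PR is given on top of the same care. In Table 1 spirometry, which guides inhaled treatment, sits at the randomisation visit, while the baseline ISWT is in the screening/baseline column. Participants are also selected on symptoms at entry (MRC dyspnoea grade 2 or more), which leaves room for regression to the mean. The documents give no figure for any of this.

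A smaller point of wording follows. Controls are offered PR only after 12 weeks of follow-up, so a window defined by the start and end of the intervention does not describe their primary measurement at 6 weeks.

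**Working it through.** **Inputs from the Sample size section.** Difference 35 m; 40 evaluable per arm; two-sided 5%; power 80%; paired t-test; 30% loss at 6 weeks; 114 randomised, 57 per arm. The SD is attributed to the feasibility study and its value is not given, so the 40 per arm cannot be reproduced directly. SDs below are back-solved or assumed.

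**Step 1: the plan's own inflation.** 40 / 0.7 = 57.1 per arm and 80 / 0.7 = 114.3 in total. The stated 57 and 114 agree apart from rounding down.

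**Step 2: the SD that makes 40 give 80% power for 35 m (noncentral t).**

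- Paired t-test, 40 pairs, standard error SD/√40: SD of change 77.0 m.
- Two-sample t-test, 40 per arm, standard error SD × √(2/40): SD of change 55.2 m.

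The two readings of 35 m therefore need different SDs. If the SD of change really is 77.0 m, a two-sample comparison with 40 per arm has about 52% power for a 35 m difference. Reaching 80% would then take 78 evaluable per arm, and 78 / 0.7 = 111.4, so 112 per arm or 224 randomised. Over an assumed range of SDs, two-sample power with 40 per arm is:

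| SD of change (m) | Power for 35 m between arms |
|---|---|
| 50 | 87% |
| 60 | 73% |
| 70 | 60% |
| 80 | 49% |
| 100 | 34% |

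**Step 3: smallest significant between-arm difference, 40 per arm.** The threshold is t(0.975, 78) × SD × √(2/40) = 1.991 × 0.2236 × SD.

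- SD 55.2 m: 24.6 m.
- SD 77.0 m: 34.3 m.

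**Step 4: the exposed window.** Let the PR arm gain g metres and controls c metres. The problem arises when g is at least 35, g − c reaches the threshold in Step 3, and g − c is below 35. The window for g − c is 24.6 to 35 m at SD 55.2 m and 34.3 to 35 m at SD 77.0 m. It closes at an SD of 35 / (1.991 × 0.2236) = 78.6 m.

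Take g exactly 35 m and assume c of 10, 20 or 30 m. The differences are 25, 15 and 5 m. Only the 25 m case is significant, and only at the lower SD (25 > 24.6, but 25 < 34.3).

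**Step 5: sensitivity to retention.** The 30% loss is described as conservative. If all 57 per arm were assessed, the threshold would be 1.981 × √(2/57) × SD = 1.981 × 0.1873 × SD: 20.5 m at SD 55.2 m and 28.6 m at SD 77.0 m. Better retention widens the window.

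**Step 6: how differently the two yardsticks behave.** With 40 per arm, suppose controls gain 20 m and PR truly adds 15 m. The PR arm's mean change then reaches 35 m with probability 50%. The observed between-arm difference reaches 35 m with probability 5% (SD 55.2 m) to 12% (SD 77.0 m). The 20 m and 15 m are assumptions.

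**The case against.** The strongest reply is that no rule in the article says clinical importance will be concluded from the PR arm alone. The 35 m figure is given descriptively with a citation, much as minimal important differences are listed for the other instruments. The only stated decision criterion is p<0.05 on the primary outcome. Defining an outcome as a participant-level change and leaving the contrast to the analysis section is ordinary practice. This stands to the extent that misuse of the label is a risk created by the wording and not a stated plan. It does not remove the mismatch: the Sample size section adopts the same pre-to-post frame and backs it with a paired t-test, so the wording is more than a loose phrase in one place.

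Several narrower replies also hold. The practice ISWT is there to deal with learning, so repetition is a weak source of control-arm gain. Optimised care is offered where possible, and inhaled treatment only where airway disease warrants it. The abstract fixes the primary window at 6 weeks, and Assessment and follow-up brings both arms to that visit, so the control arm's outcome is measurable even though the phrase defining it does not fit.

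A reader might infer that the trial could declare PR effective on a gain that controls fully share, or that differences of 5 or 15 m would pass as important. The documents do not support this. The implied test is between arms, so a fully shared gain should not usually reach p<0.05, and observed differences of 5 or 15 m fall below the significance threshold at either SD used here.

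Finally, whether the cited 35 m was derived for within-person or between-group use cannot be checked from the document. That limits how firmly 35 m can be held against the between-arm estimate.

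**Conclusion.** The point holds in a limited form. The 35 m benchmark is consistently expressed as a pre-to-post change, while the comparison that justifies randomisation is between arms, and nothing joins the two. Two things are affected.

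- **The label of clinical importance.** With 40 per arm, a significant between-arm difference of about 25 to 35 m (SD 55 m) could be called clinically important on the PR arm's own gain. At an SD of 77 m the window is under 1 m wide.
- **The powering.** Read as a between-arm difference, 35 m has 80% power with 40 per arm only if the SD of change is about 55 m; at the 77 m implied by the paired calculation, power is about 52%.

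The type I error of the between-arm test is not affected. The SDs are back-solved because the article gives none, and any control-arm gain is an assumption. It is worth correcting before results are known because the wording change is nearly free and settles how the primary result will be read.

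**What to change.** 1. **Primary outcome:** define the primary contrast as the PR-minus-usual-care difference in ISWT distance at the 6-week visit, adjusted for baseline ISWT. Replace the window tied to the intervention with baseline to the 6-week visit, so that it fits both arms.
2. **Benchmark:** state that 35 m is read against the between-arm point estimate, reported with its 95% CI. Say explicitly that the lower limit is not required to reach 35 m; under such a rule a true effect of exactly 35 m would pass only about 2.5% of the time.
3. **Within-arm results:** report the change in each arm, and the share of each arm gaining 35 m or more, as descriptive only.
4. **Incremental Shuttle Walking Test and Sample size:** align the 35 m wording with this contrast, and base the power statement on a two-sample or baseline-adjusted comparison with the SD given.
5. **Source of 35 m:** acknowledge whether the cited value was derived for within-person or between-group use.

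Cost: text changes and one recalculation, with no new data collection. The claim of clinical importance becomes somewhat harder to meet, and the recalculation may show less than 80% power if the SD of change is well above 55 m.

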#### Incremental Shuttle Walking Test

The ISWT is frequently used as an outcome measure for PR.^24^ Improvement in walking distance of 35 m during the post-PR shuttle test, measured from baseline (pre-PR) using the ISWT is considered a clinically important difference.^18^ The ISWT requires the patient to walk up and down a 10 m course, identified by two cones inset 0.5 m from either end to avoid the need for abrupt changes in direction. The speed at which the patient walks is dictated by an audio signal played on an audio device. Each participant will receive standardised instructions to: ‘Walk at a steady pace, aiming to turn around when you hear the signal. You should continue to walk until you feel that you are unable to maintain the required speed without becoming unduly breathless’.^25^ To ensure the learning effect is accounted for, a practice ISWT will be performed and the participant will receive encouragement from the physiotherapist throughout the test in an effort to increase the distance one can walk. The test is terminated when either (1) the patient indicates that they are unable to continue, (2) if the operator determines that the patient is not fit to continue or (3) the operator assesses that the patient was unable to sustain the speed and cover the distance to the cone prior to the beep sounding.^25^

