### Blinding (masking)

Due to the nature of PR, it will not be possible to blind participants to their group allocation but participants will be asked not to reveal their group during the follow-up assessments. The participant and treating clinician will be aware of treatment allocation, however, the outcome measures will be performed by staff blinded to treatment allocation and the ISWT (primary outcome) will be prioritised to reduce the risk of un-blinding. Any episodes of unblinding will be documented and reported.

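### Encouragement aimed at a longer walk is added to a self-limited primary test, with its scope unclear and contradictory statements on whether the operator knows the arm

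*Protocol article*

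**What the plan says.** All references are to the protocol article. The Incremental Shuttle Walking Test section describes the primary measurement.

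- **Pace:** "The speed at which the patient walks is dictated by an audio signal played on an audio device".
- **Instruction:** the section says "Each participant will receive standardised instructions to" walk steadily, ending with "You should continue to walk until you feel that you are unable to maintain the required speed without becoming unduly breathless".
- **Encouragement:** in the sentence that introduces the practice walk, "the participant will receive encouragement from the physiotherapist throughout the test in an effort to increase the distance one can walk".
- **Termination:** the test ends when "the patient indicates that they are unable to continue", when the operator judges the patient unfit to go on, or when "the operator assesses that the patient was unable to sustain the speed and cover the distance to the cone prior to the beep sounding".

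On who knows the allocation, Blinding (masking) states that "the outcome measures will be performed by staff blinded to treatment allocation" and that "participants will be asked not to reveal their group during the follow-up assessments". It also gives the ISWT priority at the visit and says that unblinding will be documented. The Randomisation section, however, has the allocation disclosed to the data collection team, as well as to those delivering the intervention, once baseline is complete. Assessment and follow-up lists a physiotherapist among the data collectors, and PR team lists a physiotherapist among those delivering rehabilitation.

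**The concern.** The standard instruction leaves the stopping point largely to the participant. The encouragement has the declared purpose of moving that point, and distance walked is the primary outcome. If it applies to the recorded tests, part of the measurement depends on what the operator says. The article prints fixed wording for the instruction and none for the prompts.

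Two consequences have to be kept apart. Prompting that varies by operator or visit, but not by arm, adds variance to the change score and costs some power. Prompting that is stronger in one arm shifts the treatment contrast itself, and the distances alone would not reveal it. The second needs an operator who knows or infers the arm. The article's statements on blinding do not rule that out, because two of its sections disagree.

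**Working it through.** **1. The passages side by side**

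| Question | What the article fixes |
|---|---|
| Who decides when to stop? | The participant (one criterion) or the operator's judgement (two criteria) |
| What limits prompting? | Audio-set speed; failing to reach the cone in time ends the test |
| Which walk is encouraged? | Unclear: one sentence covers both the practice walk and the encouragement, then refers only to the test |
| Does the operator know the arm? | Blinding: no. Randomisation: data collectors are told after baseline |
| Are the operator and the PR physiotherapist separate people? | Not stated |

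The route to bias is therefore open in the text, though the text does not establish that it occurs.

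**2. Inputs for the illustration** (Sample size section): 35 m difference, 40 evaluable per arm, two-sided 5%, 80% power, 30% loss, 114 randomised. The SD is attributed to a feasibility study and not printed.

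The article's total first: 80 / (1 − 0.30) = 114.3, so 114 (57 per arm) is reproduced to rounding.

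**3. Back-solved SD**

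- Two-sample, normal approximation: SD = 35 / [(1.960 + 0.842) × √(2/40)] = 55.9 m. With the t distribution it is 55.2 m.
- The article names a paired t-test. Read that way with n = 40: SD = 35 × √40 / (1.960 + 0.842) = 79.0 m (77.0 m with t). This serves as the upper end of the range.

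**4. Prompting that differs by arm, no true effect.** The standard error is SE = SD × √(2/40), which is 12.49 m for SD 55.9 and 17.67 m for SD 79.0. For an assumed extra distance b in one arm, the rejection probability is Φ(b/SE − 1.96) + Φ(−b/SE − 1.96).

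For b = 10 and SD 55.9: b/SE = 0.800, so Φ(−1.160) + Φ(−2.760) = 0.123 + 0.003 = 0.126.

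| Assumed extra distance in one arm | SD 55.9 m | SD 79.0 m |
|---|---|---|
| 0 m | 5.0% | 5.0% |
| 10 m (one shuttle; 10/35 = 29% of the benchmark) | 12.6% | 8.7% |
| 20 m (two shuttles) | 36.0% | 20.5% |

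**5. Prompting that does not differ by arm.** Suppose operator variation with SD s enters each of the two tests independently. The change score then has SD √(55.9² + 2s²).

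- s = 10 m: SD 57.6 m, power for 35 m falls from 80% to 77.5%.
- s = 20 m: SD 62.6 m, power falls to 70.5%.

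The shifts b and the spreads s are assumptions. The documents support no particular value for either.

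**The case against.** **The script may exist elsewhere.** An article condenses the full protocol, the COVID-19 section mentions a standard operating procedure for data collection, and staff were trained in the tests. This stands: the absence of a printed script is not the point. The point is what is printed, namely a prompt meant to lengthen the walk beside a self-limited instruction, with its scope unclear.

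**The sentence may cover only the practice walk.** This is a fair reading and cannot be excluded. It would leave the practice and recorded walks under different conditions, which weakens the practice walk as a control for learning. The sentence needs clarifying either way.

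**Encouragement suits a test of maximal capacity, applies to everyone and cancels between arms.** This stands as far as it goes. Equal encouragement does not bias the comparison. Even the noise may be partly counted already, since the planning SD comes from the team's own feasibility study.

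**Staff are blinded, the ISWT is prioritised and unblinding is recorded.** These measures reduce the risk. They do not settle it while the Randomisation section says the data collectors are told the allocation, and an unspoken guess would not be logged as an unblinding episode.

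**Stronger readings to avoid.** A reader might infer that ISWT distance is simply a product of how hard the operator pushes. It is not: the audio signal sets the speed, and a missed cone ends the test whatever is said. A reader might also infer that the bias is independent of who knows the allocation. It is not: every false-positive figure above requires prompting that differs by arm.

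**Conclusion.** The point holds in limited form. The article pairs a standardised, self-limited instruction with encouragement aimed at the primary outcome and leaves open whether this applies to the recorded tests. Prompting that is equal across arms and visits adds at most some noise. Bias requires an operator who knows or infers the arm, and the conflict between the Randomisation and Blinding sections, with a physiotherapist listed in both teams, leaves that possible.

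The size is unknown. On the back-solved two-sample SD, an assumed one-shuttle difference between arms takes the false-positive rate from 5% to about 12.6%, or to about 8.7% if the SD is nearer 79 m. These figures show sensitivity and do not estimate what will happen. The change is worth making because it is cheap, concerns the sole primary outcome, and uneven prompting could not be identified from the distances afterwards.

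**What to change.** Replace the encouragement clause with a rule along these lines: *No encouragement is given beyond the standard instruction. If prompts are used, they follow a fixed script with the same words and timing at the practice, baseline, 6-week and 12-week tests in both arms, delivered by staff who do not know the allocation.*

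Reconcile the Randomisation and Blinding sections on whether the data collection team learns the allocation, and state whether the physiotherapist running the ISWT is separate from the one delivering rehabilitation.

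The cost is one sentence, a correction to one of the two sections and a short operator briefing. Distances may be slightly shorter. Because the outcome is change from baseline, a switch during the trial would pair freely encouraged baselines with scripted follow-ups for some participants. The change should therefore be applied equally in both arms, its date recorded, and the effect checked in a sensitivity analysis that separates participants whose baseline preceded it.
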